### Study method

2.2

1.The patients will complete routine preoperative examination to exclude serious systemic diseases, and received enhanced valvular CT scan, so that the doctor could determine the lesion scope and vascular condition in the recipient area;2.The patients will be placed in the supine position, the middle and upper 1/3 of both lower extremities will be radiographically marked, and both lower extremities will be kept naturally straight. Iohexol injection will be injected intravenously from the middle of the elbow. A 256-slice spiral CT (Philips, USA) will be used for continuous CTA scanning from bilateral anterior superior iliac spine to bilateral lower edge of patella. CT scanning parameters will be set as 0.625 mm thickness, 120-140 kV, and 525 mA.3.CTA data preprocessing, search for puncture and define reconstruction area: obtain CTA data in DICOM format and import CTA data into 3-D15.0 software (Materialize, Belgium). After reading the data, 3-D15.0 software automatically creates a 3-D project file and uses the convert function to complete the data conversion and generate the original CTA image. Based on the original cross section, the software automatically reconstructs the continuous sectional images of sagittal plane and coronal plane to form the observation screen of 3 dimensions. The original CTA images will be scanned and observed in three orthogonal sectional views to determine the appropriate location of the perforation of the anterolateral femoral flap. Then, the 3-D reconstruction area will be restricted to 1 side of the supply area with suitable cutting struts with Crop Mask, thus reducing the workload of data segmentation in later period.4.3-D is used to reconstruct bones, blood vessels and skin: a section line is created by using the section line option in the axial window, and the gray value distribution along the line can be obtained. To better observe the transition of soft tissue, cortical bone and cancellous bone, click the option of Start Thresholding and select a certain amount of pixel gray value to segment the bone from anterior superior iliac spine to ipilateral patella. The soft tissue and some discrete voxels are then separated from the bone by means of regional growth. Select the region growth tool from the segmentation toolbar and click on the bone section to add all associated voxels to the new mask. The hip, femur, and patella will be extracted from the shape and outline of the bone at each axis view level using a multi-layer editing tool. The newly added mask will be reconstructed in 3-D to extract the individual bone model. Adjust appropriate thresholds to create a new mask, use a multi-layer editing tool on the axis view to erase irrelevant grayscale values, and retain and extract major blood vessels and perforations. The erased new mask will be reconstructed in 3-D, and the reconstructed plane mask will be duplicated. Use the Edit Mask in 3-D to edit the reconstructed 3-D model. Remove the irrelevant soft tissue with the cover lock tool. Click the erase tool to remove the selected pixels from the Mask. After the 3-D editing function is completed, close the toolbar and carry out 3-D reconstruction on the edited corresponding plane mask, so as to obtain clear blood vessels and perforating branches. Reconstruct the thigh skin, create a new mask, set the segmentation threshold, erase the gray value of irrelevant structure on the axis view, carry out 3-D reconstruction, and use the wrap function to make the reconstructed skin continuously smooth.5.3-D visualization of the model: give bone and blood vessel an opaque and skin transparency High, which allows observation and determination of bone and blood vessel through the skin. To enhance the visual effect, the target perforations and pedicles can be stained to a specific color. Based on the size and shape of the wound in the receiving area and the cutting function in the simulation option, the scope, depth and path of the flap will be simulated along the skin surface to generate a 3-D visual model of the personalized free anterolateral thigh flap.6.Simulated skin flap removal and operation: 3-D will be used to edit and process the reconstructed 3-D model before surgery. After other parts will be hidden, the designed anterolateral thigh flap will be “removed” from the 3-D model together with the vascular pedicle. The simulated data will be transferred to the intraoperative body surface of the patients, and the flap will be surgically removed to verify the accuracy of perforator location, and the anterolateral thigh flap will be transplanted and repaired for head and neck soft tissue defects.7.Routine nursing care after free flap transplantation will be given to promote wound healing. Preoperative and intraoperative measurement data will be processed and analyzed with SPSS20.0 software.

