### Interventions

2.4

Patients will be randomly divided into CTA group (n = 20), mimics group (n = 20) and CTA + mimics group (n = 20) according to the numerical table. Patients in the CTA group will receive CTA examination of lower extremities. Patients in mimics group will receive digital technology in the positioning of perforator. Patients in CTA + mimics group will receive CTA + digital technology. All the patients will receive the flap cutting and the flap making; the doctor will determine the perforation branch of the flap with 3-D visual positioning, measure the preoperative indicators intraoperatively and complete the wound repair. Finally, the survival rate, sensitivity, specificity and accuracy of the flap will be measured.

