### Measurement of outcomes

2.5

Vascular anatomy and preoperative design results of the anterolateral thigh flap will be recorded, and intraoperative and preoperative comparisons will be analyzed to explore the clinical efficacy of postoperative patients. After the completion of image digitization, 2 physicians who have been working on the anterolateral thigh flap for more than 4 years read the images in a double-blind way to evaluate whether the location, shape, and scope of the lesion of the patient has invasion or metastasis. When opinions will be different, they read the images together and agreed. Consistency analysis by CTA joint digital technology, digital technology and CTA in the defects of head and neck cancer patients in the orientation of value, when the CTA inspection found perforators preoperative and intraoperative confirmed existence is judged to be (+), when the digital technology can be worn for successful reconstruction is judged to be (+), either in the joint inspection tests to determine the (+), finally to the 3 ways to wear the positioning performance comparison.

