### Statistical analysis

2.6

Statistical analyses will be implemented by SPSS 17.0 and Microsoft Excel 2007 software. Data will be represented as mean ± standard deviation (SD). A *t*-test will be performed to compare the changes in measures within groups. Statistical significance will be considered at *P* < .05.

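### Only CTA needs surgical confirmation to be scored positive, so its specificity is 100% by construction and the three methods are scored by unequal rules

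*Protocol article*

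**What the plan says.** Section 2.5 (Measurement of outcomes) of the protocol article sets three positivity rules in one sentence:

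- CTA: "when the CTA inspection found perforators preoperative and intraoperative confirmed existence is judged to be" (+). Two conditions: seen before surgery and confirmed at surgery.
- Digital technology: "when the digital technology can be worn for successful reconstruction is judged to be" (+). One condition: the reconstruction succeeds. Surgery is not mentioned.
- Joint test: "either in the joint inspection tests to determine the" (+). Either component is enough.

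The sentence closes with the purpose: "finally to the 3 ways to wear the positioning performance comparison".

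Section 2.4 (Interventions) names the measures: "Finally, the survival rate, sensitivity, specificity and accuracy of the flap will be measured". The abstract and section 2.1 (Research object) list the same ones. Step 6 of section 2.2 (Study method) gives surgery the verifying role: "the flap will be surgically removed to verify the accuracy of perforator location". No section gives another positivity rule or a common one.

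**The concern.** A diagnostic accuracy comparison needs two separate items for each site: the test's call, and a reference result that the call is judged against. The CTA rule merges them. A perforator seen on CTA but not found at surgery does not meet the CTA definition of (+), so the error that specificity is meant to count drops out of the count. The same error made by digital technology stays (+) and counts against it.

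Specificity and accuracy are named measures, and comparing the three methods on them is the stated aim. One method's specificity would be settled by its scoring rule before any patient is enrolled, and part of any accuracy difference would come from that rule.

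**Working it through.** **Reference figure.** The article states no expected sensitivity, specificity, accuracy or prevalence, so there is nothing to reproduce. Step 1 is pure logic; the later steps rest on assumed values.

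**Step 1: the false-positive cell.** Take the surgical finding as reference and treat whatever is not (+) as (-).

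- CTA(+) = image(+) and surgery(+). The cell CTA(+)/surgery(-) is empty, so FP = 0 and specificity = TN/(TN + 0) = 1. If no surgically negative site is recorded, TN is also 0 and specificity is undefined.
- Digital(+) = reconstruction(+). This can occur at a surgically negative site, so FP can exceed 0.
- Joint(+) = CTA(+) or digital(+). At a surgically negative site CTA is never (+), so joint FP = digital FP and joint specificity = digital specificity.
- CTA sensitivity is unchanged: at a surgically positive site the confirmation condition is always met.

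**Step 2: size for two equally good methods.** Let Se and Sp be the raw sensitivity and specificity of both methods and p the share of sites with a true perforator. Accuracy = p × sensitivity + (1 − p) × specificity.

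- CTA as written: p × Se + (1 − p)
- Digital: p × Se + (1 − p) × Sp
- Difference due to the rule alone: (1 − p)(1 − Sp)

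For p from 0.7 to 0.9 and Sp from 0.6 to 0.9, the smallest value is 0.1 × 0.1 = 0.01 and the largest 0.3 × 0.4 = 0.12. Se (0.8–0.9) cancels.

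**Step 3: the joint test.** With conditionally independent errors, joint sensitivity = 1 − (1 − Se)². Joint specificity is Sp as written and Sp² if both components are scored on images alone. At Se = Sp = 0.80 and p = 0.70:

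| Method | Sensitivity | Specificity | Accuracy |
|---|---|---|---|
| CTA, as written | 0.80 | 1.00 | 0.7 × 0.80 + 0.3 × 1.00 = 0.86 |
| Digital, as written | 0.80 | 0.80 | 0.7 × 0.80 + 0.3 × 0.80 = 0.80 |
| Joint, as written | 0.96 | 0.80 | 0.7 × 0.96 + 0.3 × 0.80 = 0.912 |
| CTA or digital, images only | 0.80 | 0.80 | 0.80 |
| Joint, images only | 0.96 | 0.64 | 0.7 × 0.96 + 0.3 × 0.64 = 0.864 |

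Joint accuracy minus digital accuracy rises from 0.864 − 0.80 = 0.064 to 0.912 − 0.80 = 0.112. Joint minus CTA falls from 0.064 to 0.912 − 0.86 = 0.052. At one corner of the range (Se 0.8, Sp 0.6, p 0.7) the order of joint and CTA reverses: 0.78 against 0.74 on images alone, 0.852 against 0.86 as written.

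**Step 4: the other reading.** Suppose (+) means a verified localisation, that is, a true positive. CTA then scores p × Se = 0.7 × 0.80 = 0.56 of sites. Digital technology, with no verification required, scores p × Se + (1 − p)(1 − Sp) = 0.56 + 0.06 = 0.62. The advantage now goes to digital technology, and the scoring is still unequal.

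**The case against.** The strongest reply is that the sentence is badly translated and may condense one common rule. Section 2.5 opens by promising comparisons of preoperative with intraoperative findings, and step 6 of section 2.2 verifies the digitally planned flap at surgery, so confirmation may have been meant for every method. This lowers confidence in what the authors intended. It does not rescue the text, which attaches confirmation to CTA only. If confirmation were part of (+) for all three, none could have a false positive and specificity could not separate them. Section 2.5 also does not spell out how (+) enters the specificity calculation; that link is inferred from the named measures and the role given to surgery.

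Three stronger conclusions are tempting, and the documents do not support them.

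- *CTA would score 100% throughout and digital technology near zero on specificity.* That follows only if the sites counted are those that both methods already called positive. With 40 such sites and 32 confirmed, CTA gets 8/8 on specificity and 40/40 on accuracy, and digital technology 0/8 and 32/40. Such a set leaves out missed perforators and correct negatives. It also has both methods read the same sites, whereas the plan is "Patients will be randomly divided into CTA group (n = 20), mimics group (n = 20) and CTA + mimics group (n = 20"). CTA false negatives remain under the written rule, so CTA accuracy is not fixed at 100%.
- *Positive predictive value is a distorted endpoint.* It would be 100% for CTA by the same logic, but the protocol does not list it as a measure.
- *The rule is biased against the combination.* It raises the combination's own specificity and accuracy. The combination gains against digital technology and loses only against CTA.

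**Conclusion.** The point holds as a wrongly stated rule, not as detail left to a fuller document. On the plain reading, and with surgery as the reference, CTA specificity is 100% by construction whenever a surgically negative site exists; this needs no assumed figure. The inflation of CTA accuracy over an equally good digital method is about 0.01 to 0.12 under the assumed ranges. The true size cannot be computed from the documents.

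The joint-test figures also assume conditionally independent errors. Section 2.2 builds the reconstruction from CTA data, so the two components' errors may well coincide in part. The more they coincide, the smaller the flattery of the joint test, down to none if they coincide fully. The CTA result does not depend on this assumption.

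Confidence is high that the methods are scored unequally as written. It is moderate on the direction, because reading (+) as a verified localisation reverses the advantage.

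**What to change.** Replace the three rules in section 2.5 with one:

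- For every method, (+) or (-) at a marked site is decided from the preoperative images alone and recorded before surgery. For the joint test, state how the two image-based calls are combined.
- The intraoperative finding serves only as the reference that classes each call as true or false, with one match tolerance for all methods.
- State how surgically negative sites are ascertained. A site that surgery does not examine has no reference result; report it as unverified rather than count it as negative.

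This changes no treatment and needs no extra patients, but it is more than a change of wording: a site-level record of preoperative calls is needed, including those that surgery does not confirm. If only confirmed CTA calls have been kept for patients already treated, the stored images would have to be re-read by readers unaware of the surgical finding. The price in results is that CTA and joint specificity and accuracy will look less favourable than under the present rule.

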**Discussion::**

The anterolateral thigh flap has been widely used to repair various tissue defects and has obtained good clinical results. The extensive clinical application mainly focuses on 2 aspects, namely the study of vascular anatomy of lateral flap and the exploration of preoperative flap design technology. Perforator is the direct blood supply source of anterolateral thigh flap, so it is particularly important to study the anatomy of perforator. Therefore, this study will reveal CTA combined with digital technology in the vascular anatomy of the anterior external femoral flap and the design of the flap before and during surgery, so as to provide help for the repair of tissue defects.

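### The joint method is scored positive if either test is positive, so its true sensitivity cannot be below either component's, and higher joint sensitivity alone does not show that CTA + mimics is better

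*Protocol article*

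**What the plan says.** Section 2.5 (Measurement of outcomes) of the protocol article gives three scoring rules and a comparison:

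- CTA: "when the CTA inspection found perforators preoperative and intraoperative confirmed existence is judged to be" (+).
- Digital technology: "when the digital technology can be worn for successful reconstruction is judged to be" (+). No confirmation at operation is named.
- Joint examination: "either in the joint inspection tests to determine the" (+).
- Comparison: "finally to the 3 ways to wear the positioning performance comparison".

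The English is broken, but the natural reading of the third rule is that the joint result is positive if either component is positive.

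Section 2.4 (Interventions) lists the measures: "Finally, the survival rate, sensitivity, specificity and accuracy of the flap will be measured". Section 2.1 gives the same list as the efficacy aim. Section 2.4 also randomises separate patients to the three methods, 20 per arm. Section 2.2 builds the digital model from the CTA scan ("obtain CTA data in DICOM format and import CTA data into 3-D15.0 software"). The Discussion puts the combination at the centre of the study's purpose: "this study will reveal CTA combined with digital technology in the vascular anatomy of the anterior external femoral flap".

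**The concern.** An either-positive rule can add positives but never remove one. Every perforator that CTA or the digital model detects also counts as detected by the joint method, so the direction of the true sensitivity comparison is fixed by the scoring, whatever the second method contributes. The cost of the rule should show up as extra false positives, but the definitions blur that cost. A CTA call counts as positive only once surgery has confirmed it, so as scored CTA has no false positives. A digital call counts once the reconstruction succeeds.

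At stake is the reading of the combination the trial sets out to study. A higher sensitivity for CTA + mimics could be taken as showing better localisation when it only reflects how the joint result was defined.

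**Working it through.** The article gives no sensitivity (Se), specificity (Sp) or prevalence, so there is no figure to reproduce. All values below are assumptions.

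**1. Bounds, with no independence assumption.** For components 1 and 2 under an either-positive rule:

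- max(Se1, Se2) ≤ Se_joint ≤ min(1, Se1 + Se2)
- max(0, Sp1 + Sp2 − 1) ≤ Sp_joint ≤ min(Sp1, Sp2)

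Under conditional independence, Se_joint = 1 − (1 − Se1)(1 − Se2) and Sp_joint = Sp1 × Sp2.

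| Both components | Full overlap | Independent | No overlap, as far as possible |
|---|---|---|---|
| Se 0.70 | 0.70 | 0.91 | 1.00 |
| Se 0.80 | 0.80 | 0.96 | 1.00 |
| Se 0.90 | 0.90 | 0.99 | 1.00 |
| Sp 0.90 | 0.90 | 0.81 | 0.80 |
| Sp 0.80 | 0.80 | 0.64 | 0.60 |

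In 100,000 simulated data sets of 20, with both components read in the same patients, joint sensitivity was never below that of the better component.

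**2. A second test that carries no information.** Take CTA with Se 0.80 and add a coin flip (Se = Sp = 0.50):

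- Se_joint = 1 − 0.20 × 0.50 = 0.90.
- If CTA Sp = 0.80, Sp_joint = 0.80 × 0.50 = 0.40.
- If CTA has no false positives, as section 2.5 scores it (Sp = 1.00), Sp_joint = 1.00 × 0.50 = 0.50.

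A milder case: add a test that fires at random 20% of the time to one with Se 0.80 and Sp 0.90. Then Se = 1 − 0.20 × 0.80 = 0.84 and Sp = 0.90 × 0.80 = 0.72. Youden's index falls from 0.70 to 0.84 + 0.72 − 1 = 0.56 although sensitivity rose.

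**3. What the unequal definitions do to specificity.** If CTA Sp is 1.00 by definition, Sp_joint = 1.00 × Sp_digital = Sp_digital. Against digital technology alone, the joint method can then gain sensitivity at no cost in specificity. Against CTA alone, it is compared with a specificity of 100% that comes from the definition.

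**4. Whether accuracy would expose the problem.** Accuracy = prevalence × Se + (1 − prevalence) × Sp. For the coin-flip example with CTA Se = Sp = 0.80, CTA accuracy is 0.80 at any prevalence. The joint accuracy is:

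- prevalence 0.5: 0.5 × 0.90 + 0.5 × 0.40 = 0.65
- prevalence 0.8: 0.8 × 0.90 + 0.2 × 0.40 = 0.80
- prevalence 0.9: 0.9 × 0.90 + 0.1 × 0.40 = 0.85

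When most assessed sites do hold a perforator, accuracy can stay level or rise even with a coin flip.

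**5. Separate arms.** The bounds concern true values, or the same patients. Assume 20 evaluable perforators per arm and single-method sensitivity of 0.60 to 0.90. The exact binomial probability that the observed joint sensitivity falls below the observed single one is:

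- 2% to 3% if the components are independent
- 16% to 20% if the gain is half of that
- 39% to 44% if they overlap fully

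Since the digital model is made from CTA data, overlap is likely and the real gain may lie nearer the lower bound.

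**The case against.** The strongest reply has four parts.

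- **The result is not predetermined.** A reader might infer that the trial's observed comparison must favour CTA + mimics. The documents do not support that: section 2.4 randomises separate patients, and step 5 shows that a reversal by chance is far from rare when the components overlap. This stands, and limits the point to true sensitivity or to same-patient comparisons.
- **No sensitivity-only claim is planned.** A reader might infer that sensitivity is the main comparison, or that success will be declared on it alone. The article names no primary outcome, lists sensitivity beside survival, specificity and accuracy, and its purpose statement does not mention sensitivity. This also stands. What remains is that nothing ties a sensitivity gain to the other measures.
- **Specificity and accuracy already supply the balance.** This stands only in part. Against CTA the loss of specificity would be visible, but relative to a CTA value fixed by definition. Against digital technology it could be absent (step 3), and accuracy can rise regardless (step 4).
- **Either-positive combination is a recognised way to use two tests, and the size of the gain is informative.** This is correct. The size shows how far the methods complement each other, so it would be too strong to call the joint sensitivity worthless.

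Nor should one say that positive predictive value (PPV) must fall against both components. In the coin-flip example with CTA Sp 0.80 and 50% prevalence, joint PPV is 0.45 / (0.45 + 0.30) = 60%. That is below CTA's 0.40 / (0.40 + 0.10) = 80% but above the coin's 50%.

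**Conclusion.** The concern holds in a limited form. Under the rule in section 2.5, the joint method's true sensitivity is at least that of each component and its specificity at most that of each, with no assumption about dependence. Higher joint sensitivity is therefore not, by itself, evidence that CTA + mimics is better.

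The size depends on assumptions. An uninformative second test can add 10 points of sensitivity to an 80% test (coin flip, independence), with joint specificity of 40% or 50% depending on whether CTA specificity is taken as 80% or as 100%. Overlap through the shared CTA data would make the real gain smaller.

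The conclusion rests on the natural reading of an unclear sentence and, between arms, on each component being read in the joint arm as in its own arm. It does not extend to saying that the observed arms must favour the combination or that the investigators plan a claim on sensitivity alone. The issue should be settled before any images are scored.

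**What to change.** In section 2.5, score each method from the preoperative reading alone, then classify each call against the operative finding by the same rule for all three. Score the joint method as one integrated reading: CTA and 3-D model viewed together, one marked position per perforator. A false positive is then possible, and counted alike, for every method.

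If the either-positive rule is kept, the common classification is still needed. Otherwise CTA false positives are zero by definition and the comparison below has no fair reference. Then state that a benefit of CTA + mimics will be claimed only if sensitivity rises and false-positive perforators per patient (or PPV) are not worse than with CTA, reported with confidence intervals. Differences between the randomised arms are unpaired. Paired differences are possible only within the CTA + mimics arm, and only if both component readings are recorded there.

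The cost is a few sentences in sections 2.5 and 2.6. The two image readers are already planned, and section 2.2 already checks perforator location at operation, so no extra staff or procedure is needed. If the either-positive rule stays, two readings per patient must be recorded in the combined arm for the paired analysis. The downside is a harder bar for the joint method.
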